This study aims to determine whether the designed Immersive VR training program is better in the short term (15 sessions) and medium term (30 sessions) than physiotherapy training with exercises by Bayouk, Boucher and Leroux [39] regarding the change of measures related to static sitting, and standing balance and dynamic balance in post-stroke patients.

Secondary objectives verify the impact on quality of life and safety of the application of this type of technology.

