### 2.5. Physiotherapists Training

The interventions in both groups will be carried out by 4 physiotherapists with at least 5 years of experience in patients post-stroke management. In addition, physiotherapists will attend a 2 h training session to improve the standardization of interventions and receive a detailed procedure for each intervention to ensure they are managing patients according to trial protocols as well as recording adverse events if required. 

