The secondary outcomes will be measured with the following tools: quality of life with the ECVI-38 [54] and the adverse effects with a notebook for recording if they happen derived from the treatment.

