### 2.9. Blinding

Assessments regarding clinical recovery will be conducted by two evaluators blinded to treatment assignment. Due to the nature of the intervention, participants cannot be blinded to treatment assignment. The physiotherapist performing the intervention will also not be blinded but will be asked not to disclose the patient’s assignment status at any time or during subsequent assessments. An analyst outside the research team will enter the data into the computer on separate data sheets so that the investigators can analyze the data without having access to the allocation information.

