**Figure 3 healthcare-11-01335-f003:**
[figure not shown]
Immersive Virtual Reality scenarios.

**Table 1 healthcare-11-01335-t001:** Protocol of intervention.

Intervention Protocol	
Control Group (CG)	Intervention Group (IG)
15 min: physiotherapy treatment aimed at achieving functional improvement and increased postural control [44].	15 min: physiotherapy treatment aimed at achieving functional improvement and increased postural control [44].
15 min: static and dynamic balance training in sitting and standing according to Bayouk, Boucher and Leroux protocol [39].	15 min: static and dynamic balance training in sitting and standing through Immersive VR.

**Table 2 healthcare-11-01335-t002:** Exercises of the protocol of Bayouk, Boucher and Leroux (control group).

Exercises	Repetitions	Total Time
Stand with feet together for 10 s.	8 repetitions	2 min
Hold the tandem posture for 10 s.	8 repetitions	2 min
Get up from the chair without using arms.	3 sets of 8 repetitions	3 min
Walk forwards and backwards with one foot in front of the other.		5 min
Stay in monopodal support for 10 s.	10 repetitions	3 min

**Table 3 healthcare-11-01335-t003:** Outcomes measures.

Outcome Domain	Measures Instrument	T0	T1	T2
Sociodemographic and descriptive data	Ad Hoc questionnaire	X		
Primary outcomes				
Static balance and functional mobility	PASS	X	X	X
	BESTtest	X	X	X
Dynamic balance and gait	10 m walk test	X	X	X
	TUG	X	X	X
Secondary outcomes				
Quality of life	ECVI-38	X	X	X
Adverse effects	Open questions		X	X

T0 baseline, T1 evaluation at 15 sessions, T2 evaluation at 30 sessions. PASS- Postural Scale for Stroke Patients; TUG- Timed Up and Go; BESTest- Balance Evaluation System Test; ECVI-38- Quality of life scale for stroke.

**Table 4 healthcare-11-01335-t004:** Study period: Schedule of enrollment, interventions and assessments of this study.

STUDY PERIOD					
	Enrolment	Allocation	Post-Allocation		Closeout
Time points baseline	t	0	t15	t30	tx
Enrollment					
Eligibility screen	X				
Informed consent	X				
Allocation		X			
Assessments					
Baseline variables		X			
Post. Intervention and follow-up variables			X	X	X
Interventions					
IVR training group			X	X	
Physical therapy with Bayouk, Boucher and Leroux exercises			X	X	

IVR: Virtual Reality intervention group.

**Table 5 healthcare-11-01335-t005:** Collection of sociodemographic and descriptive data.

**Sociodemographic and descriptive data**	Age	Years
	Gender	Male/female
	BMI	Underweight/normal weight/overweight

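### The notebook rule for adverse effects admits only those put down to treatment, apparently by staff who know the arm, and does not match Table 3

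*Protocol article*

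**What the plan says.** The Introduction makes safety one of the secondary aims: "Secondary objectives verify the impact on quality of life and safety of the application of this type of technology". Section 2.7 then lists, among the secondary outcomes, "the adverse effects with a notebook for recording if they happen derived from the treatment".

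Table 3 also lists adverse effects as a secondary outcome, but gives the instrument as "Open questions", marked at T1 (15 sessions) and T2 (30 sessions). It does not limit the answers to effects of treatment, and it does not say who asks.

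On staff, section 2.5 states that "The interventions in both groups will be carried out by 4 physiotherapists", and that their training and written procedure cover managing patients to protocol "as well as recording adverse events if required". Section 2.9 adds "The physiotherapist performing the intervention will also not be blinded" and that "participants cannot be blinded to treatment assignment". The blinded evaluation in the same section is described only for the recovery measures; adverse effects are not mentioned there.

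**The concern.** An adverse event and its cause are two separate pieces of information. If the cause is judged first and decides whether the event is written down, the safety data contain only what the recorder believed to be treatment-related.

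In this trial that belief is hard to form reliably. The patients have balance impairment after stroke, the article itself ties balance loss to falls, and both arms train balance. A fall or a dizzy spell could be ascribed to the stroke, to the exercises or to the headset. A recorder who knows the arm may apply a different threshold in each.

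At stake is the secondary safety objective. Unrelated-looking events may be missing from the notebook, and a table of notebook entries by arm could suggest a difference that is not there or mask one that is. The primary balance outcomes are not affected.

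**Working it through.** No figure in the plan is in question, so the check is mainly a comparison of the text.

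**1. Is there a condition on recording?** Yes, in section 2.7: the notebook clause ties entry to the effect coming from treatment. The article gives no criteria for that judgement and names no one to make it.

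**2. Who records?** Section 2.7 does not say. Section 2.5 gives recording to the physiotherapists: "ensure they are managing patients according to trial protocols as well as recording adverse events if required". They deliver both interventions and, by section 2.9, are not blinded. That they also make the causal judgement is an inference from these two sections, though no other role is offered.

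**3. Do the three places agree?**

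| Place | Means of collection | Condition on cause | Timing | Recorder |
|---|---|---|---|---|
| Section 2.5 | Recording, if required | None stated | Not stated | Treating physiotherapists |
| Section 2.7 | Notebook | Effect must come from treatment | Not stated | Not stated |
| Table 3 | Open questions | None stated | T1 and T2 | Not stated |

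A notebook and open questions can coexist, but the article does not say whether they are one route or two, or whether the condition applies to both. At 5 sessions a week, 15 sessions take 15 / 5 = 3 weeks. If the open questions are the only unconditional route, they rely on recall over about three weeks.

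**4. What can a filter of this kind do?** For each arm:

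recorded risk = true risk × probability that an event is attributed to treatment

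so

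recorded risk ratio = true risk ratio × (attribution in VR arm / attribution in control arm).

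The document supplies none of these inputs. The values below are assumptions, chosen only to show how the filter behaves when the true risks are equal (ratio 1.0):

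| Attribution, VR | Attribution, control | Recorded risk ratio |
|---|---|---|
| 90% | 50% | 0.90 / 0.50 = 1.8 |
| 50% | 90% | 0.50 / 0.90 = 0.56 |
| 50% | 50% | 0.50 / 0.50 = 1.0 |

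For true risks of 10% to 40% in both arms, the first row gives a recorded difference of 0.10 × (0.90 − 0.50) = 4 points up to 0.40 × 0.40 = 16 points; the second row gives the same sizes with the sign reversed. In the third row the ratio is undisturbed, but half the events in each arm are not recorded.

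The distortion can therefore run either way or be absent from the ratio altogether. The loss of events remains wherever attribution is below 100%.

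**The case against.** The strongest reply has four parts.

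- **There is another route.** Table 3's open questions carry no condition on cause, so events kept out of the notebook might still be captured at T1 or T2. This stands as far as it goes. A reader might infer that screened-out events are lost for good; the article does not establish that. Equally, it does not show that the open questions are free of the condition, or that someone blinded asks them.
- **Who decides on causality is inferred.** Section 2.7 names nobody, and section 2.5 speaks of adverse events without a causal condition. This also stands, and the point is worded accordingly. The phrase in 2.5 about recording if required describes training and need not be a third competing method.
- **No comparison between arms is described.** Section 2.11 sets out hypothesis contrasts for quality of life, not for adverse effects. A reader might conclude that the rule makes the safety objective unanswerable. That is too strong: a descriptive account of effects attributed to VR would still have some value. It would remain incomplete, and in a two-arm trial readers will set the arms side by side.
- **The clause may be loose wording in a condensed article.** Possibly so, and definitions and forms may well sit in the full protocol. But the clause as printed states a rule, and a later document on analysis cannot restore events that were never collected.

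The same four physiotherapists, trained together, treat both arms. That may favour even attribution, but it does not ensure it when the arm is known.

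**Conclusion.** The point holds as a defect in a stated recording rule for a secondary objective. Read as written, section 2.7 makes entry in the notebook depend on a causal judgement. Sections 2.5 and 2.9 indicate, without saying so outright, that the judgement falls to staff who know the arm. Section 2.7 and Table 3 describe collection differently and need to be reconciled on any reading.

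The consequence is a risk of incomplete safety data and of bias in any comparison by arm. Its direction and size are unknown: the document contains no event rates and no evidence that attribution differs between arms. The ratios of 1.8 and 0.56 rest wholly on assumed attribution rates and are not estimates for this trial. It would be wrong to read the point as showing that VR will look either safer or less safe than it is.

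The change is worth making because it is cheap and because an event not collected by either route cannot be recovered at analysis.

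**What to change.** Bring sections 2.5, 2.7 and Table 3 into one rule:

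- All adverse events are recorded in both arms from allocation to T2, whatever their presumed cause.
- The same questions are put at the same times in both arms.
- Relation to treatment is a separate field, completed after the event has been recorded.
- All events are reported by randomised arm, with treatment-related events as a subset.

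The rule should also state who asks the questions and who completes the relatedness field.

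The cost is a small amendment, slightly more recording for the physiotherapists already present, and more unrelated events in the listing. The change helps only for events that occur after it takes effect. It removes the attribution filter but not all ascertainment bias, since recorders and participants still know the arm. Having relatedness judged by someone unaware of allocation, where feasible, would reduce the effect of that knowledge on the related subset.

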### 2.8. Participant Timeline

The schedule of enrollment, interventions and assessments of this study is shown in Table 4, following the SPIRIT statement [40].

### 2.9. Blinding

Assessments regarding clinical recovery will be conducted by two evaluators blinded to treatment assignment. Due to the nature of the intervention, participants cannot be blinded to treatment assignment. The physiotherapist performing the intervention will also not be blinded but will be asked not to disclose the patient’s assignment status at any time or during subsequent assessments. An analyst outside the research team will enter the data into the computer on separate data sheets so that the investigators can analyze the data without having access to the allocation information.

### 2.10. Data Collection Methods

The outcome measures set out below will be obtained prior to the intervention, at 15 sessions and 30 sessions, except for the sociodemographic and descriptive variables of the subject, which are reflected in Table 5.

### 2.11. Data Management and Statistical Analysis

Sample size: For instance, to achieve 80% power to detect differences in contrast to the null hypothesis H₀, mean difference in BESTest is equal to the limit of superiority, using a one-sided Student’s t-Test (superiority) for two independent samples, taking into account that the significance level is 5%, and assuming that the superiority limit is 7.81 units, as suggested in the article by Candance, et al., [55]. Additionally, the proportion of patients in the control group with respect to the total is 50%; it will be necessary to include 18 patients in the control group and 18 in the experimental group, a total of 36 patients in this study. Considering that the expected percentage of dropouts is 20%, it would be necessary to recruit 22 patients in the control group and 22 patients in the experimental group, a total of 44 patients in this study.

Patient characteristics and comparisons at baseline: To assess the comparability of the two groups, the characteristics of the patients assigned to each group will be presented in a table. Discrete variables will be summarized as frequencies and percentages. Continuous variables and time intervals will be summarized using means, standard deviation, or median and interquartile range. Both groups need to be homogeneous at baseline.

The statistical analysis will be carried out by an intention-to-treat analysis.

Analysis of the main objectives: Normality tests of the dependent variables were undertaken using the Kolmogorov–Smirnov test. The description of the results of the dependent variables was also performed, using either the mean and the standard deviation or the median and interquartile range, depending on the adjustment of these variables to normality. 

To respond to the main objective, with each primary result, hypothesis tests will be performed (where the alternative hypothesis is the greater efficacy of the experimental treatment compared to the conventional one), and estimates will be provided by 95% confidence intervals. In addition, the t-Student test will be used for independent samples in the parametric case and the Mann–Whitney U test for the non-parametric case.

Analysis of the secondary outcomes: For quality of life, contrasts of hypotheses will be made, and estimates will be provided by a 95% confidence interval. Furthermore, it is of interest to establish a regression model between quality of life and static balance, functional mobility, dynamic balance and gait in order to estimate their possible relationships. The strength of these relationships will be measured through the ANOVA F-test and the individual t-test. The strength of the relationship will be expressed as ORs and their 95% CI.

This project takes into account qualitative information to explore the reasons for possible dropouts through direct follow-up of patients.

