### 2.7. Outcomes

All study participants will be evaluated before starting treatment (baseline) at 15 sessions and 30 sessions. The outcome measures are compiled in Table 3. 

The parameters of balance in sitting and standing static and dynamic and in the temporospatial and kinematic parameters of gait will be obtained from the following tests and scales. 

For static balance and functional mobility, the PASS Spanish version [21,45], the BBS [34] and the BESTtest [46] have been used. 

BBS has a high relative reliability with interrater reliability estimated at 0.97 (95% CI 0.96 to 0.98) and intra-rater reliability estimated at 0.98 (95% CI 0.97 to 0.99). The absolute reliability of the BBS varies across the scale, with minimal detectable change with 95% confidence varying between 2.8/56 and 6.6/56 [41].

PASS is a 12 items performance-based scale used for assessing and monitoring postural control following a stroke. It consists of a 4-point scale where three items are scored from 0 to 3, and the total scoring ranges from 0 to 36 [45]. The minimal detectable change in subacute stroke is 2.22 points [47]; in acute stroke, 1.8 points [48]; and in chronic stroke, it is 3.2 points [49].

BESTest consists of 27 tasks, with 36 items in total. Each item is scored based on ordinal scale scoring from 0 to 3, where 3 represents best performances, and 0 represents worst performances. Scores for the total test are provided as a percentage of total points [50]. Additionally, the minimal detectable change in subacute stroke is 7.81 points [50]. 

To measure dynamic balance and gait, the TUG test [51] and the 10 m walk test [52] will be used. 

In the TUG test, the patient rises from a chair, walks three meters in a straight line, turns, returns and sits down while the examiner times the time required to perform the test. In addition, the TUG assesses the risk of falling. A score of less than 10 s indicates a low risk of falling, between 10 and 20 s indicates frailty with a higher risk of falling, and more than 20 s a high risk of falling [51]. The minimum detectable change in stroke is estimated at 2.9 s [53].

10 m walk test has an excellent interrater reliability estimated ICC = 0.87 to 0.88, and an excellent interrater reliability ICC = 0.998. The minimum detectable change is set at 0.05m/s, and a substantial change is set at 0.10m/s [52].

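### The sample size is set against a null of a 7.81-point BESTest difference, but the stated aim and primary analysis carry no margin, so the 80% power is not that of the analysis as described

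*Protocol article*

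**What the plan says.** In the protocol article, the sample size paragraph of section 2.11 seeks "to achieve 80% power to detect differences in contrast to the null hypothesis" that the "mean difference in BESTest is equal to the limit of superiority". It does so "using a one-sided Student’s t-Test (superiority) for two independent samples", at a 5% significance level with equal allocation, "assuming that the superiority limit is 7.81 units". The result is 18 patients per arm, raised to 22 per arm for dropout. No SD is given, and no expected difference other than 7.81.

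Further down the same section, the analysis of the main objectives describes a hypothesis test for each primary result, "where the alternative hypothesis is the greater efficacy of the experimental treatment compared to the conventional one". It adds that "the t-Student test will be used for independent samples in the parametric case", with the Mann–Whitney U test otherwise, and promises 95% confidence intervals. No margin appears there.

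The aim in section 1 is to find out whether the VR programme "is better in the short term (15 sessions) and medium term (30 sessions) than physiotherapy training", again without a margin. Section 2.7 uses the figure 7.81 in a different role: "the minimal detectable change in subacute stroke is 7.81 points".

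**The concern.** A null placed at 7.81 defines superiority by a margin: rejecting it means that VR is better by more than 7.81 points. A test of greater efficacy with no margin is ordinary superiority: rejecting its null means that VR is better by some amount above zero. These are different hypotheses, with different critical values and different power.

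Two things are at stake. First, the 80% is calculated for one hypothesis while the analysis text describes another, so a reader cannot take it as the power of the primary comparison. Second, the meaning of a positive trial is open. Over a wide range of observed BESTest differences, the result would be a success under one paragraph and a failure under the other, and the plan does not fix in advance which one governs.

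**Working it through.** **Inputs from the article (section 2.11):** 18 per arm, 1:1 allocation, one-sided 5%, two-sample t-test, power 80%, limit 7.81. **Not stated:** the SD, and the expected difference if 7.81 is the null. Every SD below is an assumption, or is back-solved where so labelled.

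**Reproducing the plan's figure.** The 18 per arm cannot be reproduced from the stated inputs under either reading. The margin reading lacks both the SD and the expected difference; the difference-to-detect reading lacks the SD. What can be derived is what 18 per arm implies.

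**Step 1. Distance from the null needed for 80% power.** With 18 per arm, df = 2 × 18 − 2 = 34 and the standard error is SD × √(2/18) = SD/3. From the noncentral t, one-sided 5%, 80% power requires (true difference − null)/SD = 0.846.

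**Step 2. Reading A: 7.81 is the null, as printed.** Required true difference = 7.81 + 0.846 × SD.

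The plain zero-null test at that same true difference has standardised distance 7.81/SD + 0.846. Its one-sided power follows from the noncentral t.

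| Assumed SD | True difference for 80% against 7.81 | Power of the zero-null test at that difference |
|---|---|---|
| 8 | 14.6 | over 99.9% |
| 9.2 | 15.6 | over 99.9% |
| 15 | 20.5 | 99.1% |
| 20 | 24.7 | 97.7% |

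On this reading, the 80% understates the power of the analysis as described.

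**Step 3. Reading B: 7.81 is the difference to detect and the null is zero.** The SD at which 18 per arm gives exactly 80% is 7.81/0.846 = 9.23 (back-solved). Any smaller SD gives more power and any larger SD gives less.

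| Assumed SD | One-sided power at a true difference of 7.81, 18 per arm |
|---|---|
| 8 | 89% |
| 9 | 82% |
| 10 | 74% |
| 12 | 61% |
| 15 | 45% |

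**Step 4. What counts as success.** The one-sided 5% critical value on 34 df is 1.691. At an assumed SD of 9.2:

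- Analysis text (null at zero): 1.691 × 9.2/3 = 5.2 points.
- Sizing text (null at 7.81): 7.81 + 5.2 = 13.0 points.

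An observed difference between 5.2 and 13.0 points is a positive result under one paragraph and a negative result under the other. The two cut-offs differ by 7.81 whatever the SD.

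**The case against.** The strongest reply is that 7.81 is simply the difference to detect, loosely worded as a null. Section 2.7 supports this by giving the same figure as the minimal detectable change, and the sizing sentence itself speaks of detecting differences. This is plausible. But it concedes that the printed null is wrong, and it leaves the 80% resting on an SD that the article does not give.

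A second reply is that the analysis text never writes a null of zero. A t-test can be run against a shifted null, and a Mann–Whitney test can be run after shifting one arm by 7.81; the article is condensed and its analysis plan is not shown. This stands as a limit on the claim. A reader might infer that the 80% belongs to a test the trial will certainly not run, and the document does not go that far. It shows that the margin is not carried from the sizing into the analysis or the aim, whose plain reading is ordinary superiority.

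A third reply is that the mismatch is harmless for power. On the literal reading it is indeed conservative for a plain superiority claim, as step 2 shows. That does not settle which result counts as success, and under the difference-to-detect reading the comfort disappears at an SD above about 9.2.

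The absence of margins for the other primary scales adds little. Sizing a trial on one outcome is ordinary, and the article introduces the calculation as an example.

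**Conclusion.** The inconsistency is real and lies within section 2.11: the sizing uses a null at 7.81, while the analysis and the aim carry no margin. The stated 80% is not the power of the analysis as described. At an assumed SD of 9.2, the threshold for success is 5.2 or 13.0 points depending on the paragraph.

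The direction of the error depends on the intended meaning:

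- If 7.81 is the null, the plan needs an unstated true difference of 7.81 + 0.846 × SD, and a plain superiority test would have about 98% power or more for assumed SDs of 8 to 20.
- If 7.81 is the target, the null is misprinted, and at least 80% power holds only for an SD up to about 9.2.

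Two stronger readings are not supported. A reader might infer that the trial is underpowered; the article does not establish this, because the first reading implies ample power for a plain test and the second turns on an SD that is not given. A reader might also infer that power is only 5% at a true difference of 7.81. That applies only if the margin is actually tested, since the rejection rate at the null is then the 5% significance level. It does not apply to the margin-free analysis that the article describes.

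The power figures assume a two-sample t-test with a common SD and 18 analysed patients per arm.

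**What to change.** Use one hypothesis in both paragraphs of section 2.11.

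- **To match the aim:** write the null as a mean BESTest difference of 0 or less, name 7.81 as the difference to be detected, state the SD used and its source, and restate the power of 18 per arm on that basis.
- **If a margin is truly intended:** write the primary BESTest analysis as a test of a difference of 7.81 or less, claim superiority only if the lower confidence limit (at the level matching the one-sided test) exceeds 7.81, and state the expected difference and the SD. The aim should then say that VR must be better by more than the margin.

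The cost is rewording and one recalculation. The correction itself adds no patients, but at the fixed sample size the restated power may fall below 80%: under the first option it does so at any SD above about 9.2. The sponsor would then have to accept the lower power or revisit the sample size.

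### Recruiting 22 per arm leaves slightly fewer than the required 18 per arm at the plan's own 20% dropout; 44 recruits cover about 18%

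*Protocol article*

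**What the plan says.** The sample-size paragraph of section 2.11 (Data Management and Statistical Analysis) of the protocol article sets the calculation out in three steps.

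- **Evaluable number.** For 80% power at a 5% level, "using a one-sided Student’s t-Test (superiority) for two independent samples" on the BESTest, with a superiority limit of 7.81 units and equal allocation, "it will be necessary to include 18 patients in the control group and 18 in the experimental group, a total of 36 patients".
- **Expected loss.** "Considering that the expected percentage of dropouts is 20" per cent.
- **Recruitment target.** On that basis "it would be necessary to recruit 22 patients in the control group and 22 patients in the experimental group", 44 patients overall.

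The paragraph gives no formula for the dropout allowance and no rounding rule. It also states no standard deviation and no assumed true difference. The same section says that the analysis will be by intention to treat.

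**The concern.** A dropout allowance has one purpose: after the expected loss, the number the power calculation calls for should still be there. The paragraph supplies all three quantities (18, 20% and 22), so a reader can test whether they fit, and they do not quite. Applying the stated loss to the stated target gives fewer than the stated requirement.

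What is at stake is the accuracy of a headline figure. Readers of the protocol will take 44 as the number that protects 80% power when one patient in five is lost. Strictly, it protects that number of patients only at a somewhat lower loss.

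**Working it through.** **Inputs, all from the sample-size paragraph of section 2.11:** 18 evaluable per arm (36 total), dropout 20%, target 22 per arm (44 total), one-sided two-sample t-test, 5% level, 80% power, equal allocation.

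**1. Reproducing the plan's 22.** Two routes lead there:
- Multiply by one plus the dropout rate: 18 × 1.2 = 21.6, rounded up to 22.
- Divide by the retained fraction: 18 / 0.8 = 22.5, rounded down to 22.

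The article does not say which was used. Neither preserves 18 at 20% loss. The first uses the wrong inflation factor; the second rounds a minimum downwards.

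**2. What 44 recruits leave at 20% loss.**
- Per arm: 22 × 0.8 = 17.6, against 18.
- In total: 44 × 0.8 = 35.2, against 36, a shortfall of 0.8 of a patient.

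**3. What dropout 44 recruits do cover.** 1 − 18/22 = 4/22 = 18.2%.

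**4. What 20% dropout needs.**
- Per arm, rounded up: 18 / 0.8 = 22.5, so 23 per arm and 46 in total; 46 × 0.8 = 36.8.
- On the total: 36 / 0.8 = 45; 45 × 0.8 = 36.0. An odd total cannot be split equally, so 1:1 allocation with equal arms leads to 46.

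**5. Effect on power.** The article gives no standard deviation or true difference, so the 18 cannot be re-derived. The standardised effect d has to be back-solved, which is an assumption. Power is P(T > t(0.95; 2n − 2)), with T noncentral t on 2n − 2 degrees of freedom and noncentrality d√(n/2). The value of d depends on where the unrounded requirement lay before it became 18:

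| Assumed unrounded requirement per arm | d giving 80% there | Power at 17.6 per arm |
|---|---|---|
| exactly 18 | 0.846 | 79.2% |
| 17.6 | 0.856 | 80.0% |
| just above 17 | 0.871 | 81.2% |

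At the expected number of completers, power therefore lies between 79.2% and 81.2%. The largest shortfall from 80% is 0.8 of a percentage point.

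**6. Chance of keeping 36.** Suppose each patient drops out independently with probability 0.2 (a further assumption). The probability that at least 36 remain is then about 47% with 44 recruits, 59% with 45 and 69% with 46.

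**The case against.** The case for leaving the figure alone has four parts.

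**The gap is a fraction of a patient.** Twenty per cent of 22 is 4.4. The nearest whole number of losses is 4, and 22 − 4 = 18, exactly the requirement. This stands as a statement of size, but it does not make the figures agree. On the total, 20% of 44 is 8.8; the nearest whole number is 9, and 35 remain. An allowance meant to secure a minimum should not depend on which way the loss happens to round.

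**The cause is not documented.** A reader might infer that the plan multiplied by 1.2 where it should have divided by 0.8. That fits, but so does dividing by 0.8 and rounding down, and the article shows no formula. The objection stands as to the cause. It does not touch the result, since both routes leave 17.6 per arm.

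**A power loss is not shown.** A reader might infer that the trial has 79% power, or 78% if only 17 per arm remain, in place of 80%. Those figures hold only if 18 per arm gives exactly 80.0%. If 18 was rounded up from a value between 17 and 18, power at 17.6 per arm is anywhere from 79.2% to 81.2%. The objection stands: a definite fall below 80% cannot be claimed from what the article states.

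**Intention to treat and the meaning of 20%.** Patients who stop treatment but are still assessed are not lost to an intention-to-treat analysis, so fewer than 20% might be unevaluable. That may turn out true in practice. However, the paragraph inflates the sample for dropouts, so it counts them as lost, and the inflation has to be right on that footing. It is also fair that 20% is a forecast. A reader might infer that both the target and the dropout rate are misstated, but the article does not offer 20% as the limit the trial can tolerate. It is enough to adjust one of the two.

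**Conclusion.** The inconsistency is real and small. On the article's own inputs, 44 recruits with 20% dropout leave an expected 35.2 patients, against the 36 it calls necessary. The target matches about 18% dropout. This part rests on no assumption beyond the stated 18, 20% and 22.

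The consequence for power is slight and uncertain. It is at most 0.8 of a percentage point at the expected dropout, and possibly nothing below 80%, depending on an effect size and rounding that the article does not give. The documents do not support a description of the trial as materially underpowered on this account, nor a firm statement of which arithmetical slip occurred. No test, analysis set or interpretation changes. It is a minor correction to a figure that readers will rely on.

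**What to change.** Either of two changes settles it:

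- **Keep 44** and state that 22 per arm retains 18 per arm with dropout up to about 18% (4 of 22). This costs one sentence and no extra patients.
- **Keep 20%** and correct the target to 23 per arm, 46 in total (18 / 0.8 = 22.5, rounded up). This costs two further patients.

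In either case, show the formula and the rounding used for the allowance, so that the step from 18 to the target can be followed.
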